## 4.2. Measurements

### 4.2.1. Respiratory infection symptoms (I, II,III)

#### Data collection

Data will be collected throughout the study. In the validation study physicians will follow the inclusion criteria and each patient that meets possible inclusion for case or control, after accepting study inclusion demographic and clinical characteristics (age, gender, education, smoking habits, allergic diseases) will be collected before delivering the questionnaires. This information will be kept. The 6 days questionnaire of respiratory infections (**Attachment1**), and the SF-36(**Attachment 2**) and an pre-paid envelope with the Hospital/health center address will be given to the participant, explaining to him how it should be filled and that they could send it to the investigators by mail or left in the institution.

In the respiratory infection in athletes(I) a daily questionnaire will be provided and participants will fill in the questionnaire if they fill sick and daily until the symptoms have ceased. At the end of the 3 months follow-up questionnaires will be retrieved.

In the elderly population a simplified symptoms diary was provided, where they everyday coated which of the respiratory symptoms they had.

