## **4.1.2. Respiratory Infection susceptibility in athletes-illness prone profile (II)**

This is a prospective, three month follow-up, cohort study to evaluate the risk factors for respiratory infection. A group of swimmers from a Porto sports team (Futebol Clube do Porto), from a high competition level and active during the follow-up period, which is coincident with a pre-competition season and higher incidence of respiratory infections (from January to March). During this time participants will be followed for respiratory infections episodes through a daily respiratory infections questionnaire, which is filled in when they began respiratory infections symptoms and then everyday during the scheduled-time illness. Acute respiratory infection number, duration severity of each episode will be characterized. All potential risk factors for respiratory infections will be evaluated at baseline and at the end of the study, except for urine analysis which will be collected every week and during the respiratory infection episode to establish an eventual association between changes of urinary metabolome in and outside the infection period.

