### **Procedures**

Participants recruited in the previous project "*Mechanisms of airway damage in elite swimmers*" and all those that fill in the inclusion criteria, accept to participate and sign the informed consent will be evaluated at baseline.

In baseline the following characteristics and potential risk factors for respiratory infections will be screened:

- demographic data; full clinical history (namely asthma, respiratory or cardiovascular disease); chronic medication (any medication taken oral or inhaled); time of exercise practice and intensity of the trainings; immunization status and influenza vaccine; use of pro-biotics or vitamin supplements

- anthropometric and bio-impedance measures;
- nutritional state assessment and nutritional questionnaires (see description in measurements)
- sleep quality assessment questionnaires (**Attachment 3**) and anxiety symptoms questionnaire (Zung Self Rate Anxiety Scale- **Attachment 4**)
- lung function (espirometry), airway inflammation evaluated by induced sputum evaluation, airway hyper-responsiveness (methacholine provocation testing), bronchial challenge with inhaled capsaicin, exhaled nitric oxide measurement (*performed in the “Mechanisms of airway damage in elite swimmers” project-accepted by the ethical commission Centro Hospitalar de São João Attachment 5*)
- cholinergic-parasympathetic system measure by pupillometry response (*performed in the “Mechanisms of airway damage in elite swimmers” project-accepted by the ethical commission of Centro Hospitalar de São João Attachment 5*)
- blood withdraw for inflammatory cytokines measurement
- exhaled breath condensate, exhaled breath
- urine collection for metabolome measurements

During the follow-up it will be monitored through a respiratory infections questionnaire the episodes of respiratory infections, duration, severity and quality of life impact. A diary of all missed trainings will be kept during the follow-up period. Urine samples will be obtained every week and during the infections period.

Participants will also be submitted to a nutritional 24h dietary recall interview twice a month. The first one will occur at baseline and will be performed face-to-face with the investigator, so that the participant understand the purpose of the interview and also could be trained in the procedure. The following recalls will be assessed by telephone.

At the end of the follow-up period participants will perform:

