- anthropometric and bio-impedance measures;
- nutritional state assessment and nutritional questionnaires;
- sleep quality assessment questionnaires and anxiety symptoms questionnaire (Zung Self Rate Anxiety Scale-- **Attachment 4**);

All variables will be assembled at the end of the study and individuals with respiratory infections during this period will be compared with those without the outcome. Associations will be performed *a posteriori* between urine metabolome analysis and the days with respiratory infections and before/after an infection episode.

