#### Respiratory infections symptoms questionnaire (I, II)

Respiratory infections symptoms questionnaire has 21 items, organizes in a 7 point Likert-type severity scale (from 1, very mild to 7, severe and one 0, without symptoms). Two items are used to classify the global-severity-today (how sick do you feel today and compared to yesterday I fell my cold is...). The severity score includes 10 items classifying in the last 24h respiratory symptoms (runny nose, plugged nose, sneezing, sore throat, scratchy throat, cough, hoarseness, head congestion, chest congestion, feeling tired) and 9 items of quality of life impact (think clearly, sleep well, breath easily, walk, climb stairs, accomplish daily activities, work outside home, work inside home, interact with other, live your personal life) [10, 40].

An acute respiratory infection episode is defined by having all these items for at least 2 days:

- answering "Yes" to either: "Do you think you have a cold?" or "Do you think you are coming down with a cold?"
- reporting at least 1 of 4 cold symptoms (or synonyms) (nasal discharge (runny nose); nasal obstruction (plugged or congested); sneezing; or sore (scratchy) throat)
- scoring at least 2 points on the Jackson scale (Jackson score is calculated by summing 8 symptom scores (sneezing, headache, malaise, chilliness, nasal discharge, nasal obstruction, sore throat and cough), rated as 0=absent, 1=mild, 2=moderate, and 3=severe.

From the first day of acute respiratory infection day and forward each participant fills out a daily WURSS until they answer "No" to the question "Do you think that you are still sick with this respiratory infection?" for 2 days in a row. The last day the participant answers "Yes" and fills out a WURSS instrument will be the last day classified as acute respiratory infection.

Daily WURSS summary scores are calculated by summing scores of individual item scores, excluding the first and last items, which have categorically different reference domains, and are analyzed separately. Summary scores of ARI illness episodes are calculated by summing daily scores.

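### In Study II an infection that a swimmer does not record cannot be told from good health, because the questionnaire has no well-day entry and no planned contact asks about illness

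*Protocol*

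**What the plan says.** Section 4.1.2 describes the swimmer cohort: "This is a prospective, three month follow-up, cohort study to evaluate the risk factors for respiratory infection". Follow-up uses a daily respiratory questionnaire "which is filled in when they began respiratory infections symptoms and then everyday during the scheduled-time illness". Section 4.2.1, Data collection, repeats this for the athletes: "participants will fill in the questionnaire if they fill sick and daily until the symptoms have ceased". On collection it says: "At the end of the 3 months follow-up questionnaires will be retrieved".

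The analysis in Section 4.1.2, Procedures, is a two-group comparison: "individuals with respiratory infections during this period will be compared with those without the outcome". Number, duration and severity of episodes are also to be characterised.

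Other contacts are planned in the same section. "Urine samples will be obtained every week and during the infections period". There are also dietary recalls twice a month (by telephone after baseline), a diary of missed training and an end-of-study assessment. None of these is said to record whether the swimmer has been ill.

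The detailed instrument text in Section 4.2.1 (Respiratory infections symptoms questionnaire, I and II) requires the criteria on at least 2 days for an episode. It closes the episode differently from the Data collection text: daily forms continue until the swimmer answers No to still being sick "for 2 days in a row. The last day the participant answers" Yes and completes a form is the last day of the infection.

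**The concern.** A record that exists only for ill days gives no evidence of having been well. An empty questionnaire can come from 12 healthy weeks or from an illness that was never written down, and the two-group comparison places both swimmers on the uninfected side. This affects infection yes/no and the number of episodes, on which the risk-factor models of Section 4.3.2 depend.

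It also reaches the laboratory work. Section 4.2.10 restricts the swimmers' urine analysis to samples related to the infection outcome, and Section 7 says only infection-period urine will be analysed. An unrecorded infection means the sample is not chosen, or serves as an infection-free reference in the planned before/after comparison.

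The gap lies in data capture. If well and unobserved weeks are not distinguished at the time, no analysis rule written later can separate them.

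**Working it through.** **1. What is observed.** Four cases, read against the sections above:

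- Healthy for the whole period: no pages filled in.
- Stays in the study, falls ill, never opens the questionnaire: no pages filled in, weekly urine and recalls continue. Nothing in the described data separates this swimmer from the first.
- Leaves the squad: urine, recalls, training diary and final assessment stop. The departure is visible.
- Stops part-way through an episode after 2 qualifying days: already counts as infected. Only duration and severity suffer.

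The defect is therefore confined to the second case and to later episodes that go unrecorded in the same way. Study III shows the missing element: Section 4.1.3 describes monthly calls asking whether participants were still in the trial and had been sick.

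**2. The plan's own figures.** The sample size text under Section 4.3.2 gives 40 swimmers, 40% infected, alpha 0.05 and power 35%. Expected infected: 40 × 0.40 = 16. The 35% cannot be reproduced from these inputs, because no comparator rate, group split or sidedness is given. With 20 v 20 and a two-sided test, for instance, it needs a comparator of about 17% or 65%. The point does not rest on that figure.

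**3. Effect on the infection risk.** Let m be the share of infected swimmers whose infection goes unrecorded. The documents give no value, so m is an assumption. Observed risk = 0.40 × (1 − m).

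| m | observed risk | recorded infected, of 40 |
|---|---|---|
| 0% | 40% | 16 |
| 10% | 36% | 14.4 |
| 20% | 32% | 12.8 |
| 30% | 28% | 11.2 |

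**4. Effect on associations.** With m1 unrecorded in the exposed and m0 in the unexposed, observed RR = true RR × (1 − m1)/(1 − m0).

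- Factor with no effect, equal m: RR stays 1.00.
- Factor with no effect, 30% v 10%: 0.7/0.9 = 0.78. At 40% risk in both groups the observed risks are 28% and 36%, so OR = (0.28/0.72)/(0.36/0.64) = 0.69.
- The same shares reversed: RR 0.9/0.7 = 1.29, OR 1.45.
- Assumed true risks 55% v 25% (RR 2.20, OR 3.67): equal 20% loss leaves RR at 2.20, lowers OR to 3.14 and lowers 20 v 20 power from 49% to 37%. Loss of 30% v 10% gives RR 1.71 and OR 2.16; 10% v 30% gives RR 2.83 and OR 4.62.

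The sign of the bias follows the assumed pattern of non-recording, and the documents say nothing about that pattern.

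**5. The closing rules.** For one unbroken, fully recorded illness, both rules give the same last day. They part when symptoms lapse for a day and return. Under the 2-day rule the episode continues, whereas a swimmer who stopped at the first well day may not resume. A swimmer following the Data collection text also leaves no closing No answers, so recovery and abandoning the form look alike. Section 4.1.2 adds a third wording tied to a scheduled illness time.

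**The case against.** The protocol nowhere says that a swimmer who drops out is counted as infection-free. A reader might infer it from the two-group comparison, but the text does not support it. A leaver whose forms are not retrieved has a missing outcome, the interrupted contacts would reveal the departure, and the handling of such swimmers may properly be left to the SAP. Stopping during an episode does not turn an infected swimmer into an uninfected one either. All of this stands, and it limits the point to swimmers who remain in the study.

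A reader might also infer that non-recording makes harmful factors look protective. That holds only for one direction of differential recording; the opposite direction exaggerates risk, and equal recording leaves a null factor null.

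The requirement for urine during infection suggests the team would hear of episodes as they occur. It does suggest that, but no route for reporting an illness is described while the forms stay with the swimmer.

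On the closing rules, the Data collection sentence can be read as shorthand for the detailed rule, and it defines no episodes, so it cannot be said to split one illness into two. Aligning the wording is still needed, because swimmers will follow whichever instruction they are given.

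Finally, this is one small exploratory cohort with a stated power of 35%, and a loss of 1.6 to 4.8 recorded infections is of the same order as the binomial standard deviation, √(40 × 0.4 × 0.6) = 3.1. That tempers the importance, but sampling variation does not cancel a systematic loss.

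**Conclusion.** As written, non-recording in Study II cannot be distinguished from absence of infection among swimmers who stay under follow-up. The infection risk and the number of episodes can only be understated by this. Associations with risk factors can move either way, and the selection of urine samples can be misdirected. The size is unknown. The illustrations rest on assumed non-recording shares of 10% to 30% of infected swimmers and, for one set of associations, on assumed true risks. They show what such losses would do and do not predict them. The two closing rules in Section 4.2.1 are a separate, smaller inconsistency that touches duration. The change is worth making because it is cheap and because the information cannot be rebuilt afterwards.

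**What to change.** - At each weekly urine collection, ask whether the swimmer has been ill since the last contact, and log the week as ill, well or not observed. Use the twice-monthly recall calls as back-up when a collection is missed.
- Do not class a swimmer with unobserved weeks and no recorded infection as uninfected for the full 12 weeks. Either treat that outcome as missing in the planned logistic model, or use a rate or complementary log-log model with observed weeks as exposure. Adding an offset for observed weeks to the logistic model would not give the intended adjustment. The missing-outcome route keeps infected swimmers with gaps and drops uninfected ones with gaps, so it tends to raise the estimated risk; the second route is preferable if gaps are common.
- Make the Data collection text and Section 4.1.2 refer to the 2-day closing rule in the questionnaire section, so that every swimmer receives one instruction.

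The cost is one question at contacts already planned, one column in the data file and possibly a different model. Some swimmers will contribute fewer than 12 observed weeks. The weekly question will flag a missed illness but cannot supply its daily scores, so severity stays missing for those episodes.

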#### Respiratory infections symptoms questionnaire (I, II)

Respiratory infections symptoms questionnaire has 21 items, organizes in a 7 point Likert-type severity scale (from 1, very mild to 7, severe and one 0, without symptoms). Two items are used to classify the global-severity-today (how sick do you feel today and compared to yesterday I fell my cold is...). The severity score includes 10 items classifying in the last 24h respiratory symptoms (runny nose, plugged nose, sneezing, sore throat, scratchy throat, cough, hoarseness, head congestion, chest congestion, feeling tired) and 9 items of quality of life impact (think clearly, sleep well, breath easily, walk, climb stairs, accomplish daily activities, work outside home, work inside home, interact with other, live your personal life) [10, 40].

An acute respiratory infection episode is defined by having all these items for at least 2 days:

- answering "Yes" to either: "Do you think you have a cold?" or "Do you think you are coming down with a cold?"
- reporting at least 1 of 4 cold symptoms (or synonyms) (nasal discharge (runny nose); nasal obstruction (plugged or congested); sneezing; or sore (scratchy) throat)
- scoring at least 2 points on the Jackson scale (Jackson score is calculated by summing 8 symptom scores (sneezing, headache, malaise, chilliness, nasal discharge, nasal obstruction, sore throat and cough), rated as 0=absent, 1=mild, 2=moderate, and 3=severe.

From the first day of acute respiratory infection day and forward each participant fills out a daily WURSS until they answer "No" to the question "Do you think that you are still sick with this respiratory infection?" for 2 days in a row. The last day the participant answers "Yes" and fills out a WURSS instrument will be the last day classified as acute respiratory infection.

Daily WURSS summary scores are calculated by summing scores of individual item scores, excluding the first and last items, which have categorically different reference domains, and are analyzed separately. Summary scores of ARI illness episodes are calculated by summing daily scores.

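### Study II's infection episode cannot be derived as defined from the questionnaire items listed: the cold questions, two or three Jackson symptoms and a scale conversion are missing

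*Protocol*

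**What the plan says.** Section 4.1.2 follows swimmers' episodes over three months through a daily respiratory infections questionnaire, started when symptoms begin. Section 4.2.1, Data collection, likewise has swimmers complete a daily questionnaire when they feel sick, and adds: "At the end of the 3 months follow-up questionnaires will be retrieved".

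The subsection of 4.2.1 headed for Studies I and II describes that instrument: "Respiratory infections symptoms questionnaire has 21 items, organizes in a 7 point Likert-type severity scale", with 0 for no symptom. It is made up of two global items, ten symptoms and nine impact items. The ten symptoms are: "runny nose, plugged nose, sneezing, sore throat, scratchy throat, cough, hoarseness, head congestion, chest congestion, feeling tired".

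The same subsection then sets the case definition: "An acute respiratory infection episode is defined by having all these items for at least 2 days". The criteria are:

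- (a) a yes to either having a cold or coming down with one;
- (b) at least one of four cold symptoms (nasal discharge, nasal obstruction, sneezing, sore or scratchy throat);
- (c) "scoring at least 2 points on the Jackson scale", where the eight summed symptoms are "sneezing, headache, malaise, chilliness, nasal discharge, nasal obstruction, sore throat and cough", each "rated as 0=absent, 1=mild, 2=moderate, and 3=severe".

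The daily WURSS is then completed from the first day of the episode until a stop question is answered no on two successive days. Sections 4.1.1 (Procedures and Validation) add headache, body ache and fever to the questionnaire, but in the Study I text.

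**The concern.** The definition uses data that the listed instrument does not hold. Both cold questions are absent, and so are two or three of the eight Jackson symptoms. The remaining five are graded on a different scale, with no conversion given.

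Infected versus not infected is the comparison planned at the end of Section 4.1.2 and the outcome of the logistic models in Section 4.3.2. Episode severity depends on it too, because daily scores are summed over the days of an episode. It also decides which urine samples are analysed (Sections 4.2.10 and 7).

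The study is small. Section 4.3.2 gives 40 swimmers and 40% infected, so 0.40 × 40 = 16 expected cases, with a stated power of 35%. Each reclassified swimmer is 1/16, about 6% of the cases. Forms come back only after three months, so a question that was not asked would be noticed too late to repair.

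**Working it through.** The protocol states no figure on this point, so there is none to reproduce. The check matches items and then counts answer patterns. All inputs come from the Section 4.2.1 subsection for Studies I and II.

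**Step 1. Match what the definition needs to what is listed.**

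| Needed for the episode | Listed item (0-7) |
|---|---|
| Sneezing | sneezing |
| Nasal discharge | runny nose |
| Nasal obstruction | plugged nose |
| Sore throat | sore throat; scratchy throat |
| Cough | cough |
| Headache | none (added in the Study I text only) |
| Malaise | none (feeling tired is nearest, but is not equated with it) |
| Chilliness | none |
| Either cold question | none |

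Five of the eight Jackson symptoms are listed. Three are not, or two if the Study I additions carry over. The two global items ask how sick the person feels and how today compares with yesterday. Neither asks whether a cold is present.

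**Step 2. Count the patterns that truly meet (b) and (c), on the 0-3 scale.** There are four cold symptoms and four other Jackson symptoms.

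- At least one cold symptom: (4^4 − 1) × 4^4 = 255 × 256 = 65,280.
- Of these, total below 2: one mild cold symptom and nothing else = 4.
- Qualifying: 65,280 − 4 = 65,276.

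**Step 3. Count those missed when only the five listed symptoms are summed.** The five-item sum is below 2 only for one mild cold symptom without cough (4 ways). The true total still reaches 2 if at least one of the three uncollected symptoms is present (4^3 − 1 = 63 ways).

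- Missed: 4 × 63 = 252, and 252 / 65,276 = 0.4%.
- With headache collected: 4 × (4^2 − 1) = 60, and 60 / 65,276 = 0.1%.

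**Step 4. Look from the five listed symptoms alone.** Patterns with a cold symptom number 4^5 − 4 = 1,020. Of these, 1,016 already score 2 or more, and 4 depend on uncollected symptoms.

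**Step 5. The scale.** On 0-7 there are 8^5 − 8 = 32,760 five-item patterns with a cold symptom. Assume a conversion that keeps 0 at 0 and sends every non-zero score to 1, 2 or 3. Any two non-zero items then reach 2. Only a cold symptom standing alone is undecided: 4 × 7 = 28 patterns. If raw 0-7 scores were summed instead, one cold symptom scored 2 out of 7 would satisfy (c).

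**Step 6. The cold question.** Criterion (a) is mandatory and has no listed source, so no rule applied to the 21 items yields it. By Step 4, (c) adds little once (b) holds, at least in pattern terms. That leaves (a) as the criterion that most separates a cold from other nasal or throat symptoms.

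**The case against.** The strongest reply is that the subsection describes two steps: the cold questions and Jackson ratings identify an episode, and the WURSS then measures its severity and length. The wording that starts the daily WURSS on the first episode day supports this, and so does the stop question, which is also outside the 21 items. On that reading the Jackson ratings are collected directly on 0-3 and no conversion is needed. The swimmers' form is not reproduced, and Attachment 1 is only a title. Headache may also be covered by the Study I additions, since both texts cite the same sources.

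Part of this stands. A reader might infer that the items are never asked, or that the outcome cannot be computed at all. The documents do not show either, because the questions may sit on an unnamed form. What does not stand is that the text already settles the matter. Section 4.1.2 monitors episodes through the respiratory infections questionnaire, and no section or attachment title supplies a second Study II form for the first step.

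A reader might also infer that close to half of borderline episodes are lost. Of patterns totalling exactly 2, 36 − 10 = 26 include a cold symptom, and 4 × 3 = 12 of these (46%) fall below 2 on the five listed items. At a total of exactly 3 it is 24 of 100. The arithmetic is right, but it looks only at the threshold. Across all qualifying patterns the share is 0.4%. Mild patterns may be commoner in practice than an equal count implies, so neither percentage estimates a frequency in swimmers.

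**Conclusion.** The point holds as a mismatch between outcome and instrument: the episode cannot be derived as defined from the items the protocol lists. The three gaps differ in weight.

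- **Cold question.** This is the main gap. It is mandatory, and no listed item yields it.
- **Scale.** No conversion is stated. Under the Step 5 assumption the choice matters only for a lone cold symptom, but raw summing would lower the bar to a single score of 2 out of 7.
- **Missing symptoms.** The effect is confined to a lone mild cold symptom without cough: 252 of 65,276 patterns, or 60 if headache is collected.

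The counts weight every pattern equally and apply criteria (b) and (c) to a single day. They show where the definition is undecided, not how often that will happen. The conclusion also depends on the swimmers' form matching the listed items, which cannot be checked. If the form already carries the questions and ratings, what remains is to name it. This is a measurement definition that the protocol itself fixes, so it is not detail left to a statistical analysis plan.

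**What to change.** Before follow-up starts, put the two cold questions and all eight Jackson symptoms, rated 0-3, on the Study II daily form. Name that form in Section 4.2.1, both under Data collection and in the questionnaire subsection for Studies I and II. State there whether the headache, body ache and fever additions apply to Study II.

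If the form cannot change, define the episode on the items it does collect, with a stated cut-off on the 0-7 scale, and say what replaces the cold question.

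The cost is a few more lines for the swimmer on each sick day. The protocol is dated 10 December 2012 and follow-up runs January to March, so the change has to be made promptly.
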